### Sample size calculation

The most relevant information on the standard deviation available was from the feasibility study. Even though the sample of this feasibility was small (*n* = 5), the participants and the environment in which the study was conducted and the measurements taken are directly in alignment with that for the proposed RCT. Each patient was assessed at 2 h. The reported Area Under the Curve (AUC) score, as a proportion of the 42 day potential AUC score of 420 (42 days with maximum score of 10; 10 cm Visual Analogue Scale (VAS) [53], at 2 h post had a mean of 0.188 and standard deviation of 0.261 cm, based on the observed AUC scores (i.e. mean and standard deviation of the 5 AUC scores of the participants were calculated). The large effect size 0f 0.8 was determined based on discussions among the study investigators and other experts in the field. A large effect size was believed to be needed since a substantive morning stiffness improvement would be required to lead to potentially important improvements in subsequent daily functioning; whereas smaller changes in effect size were not believed to be substantive enough to impact these activities of daily functioning. To detect an effect size of 0.8, with power of 80% and level of significance of 0.05, a sample size of 28 participants per group will be required. No dropouts in the pilot were experienced and none are expected in the main study given the short duration of the study; however a 5% dropout is assumed and a sample size of 30 per group will be recruited.

No dropouts in the feasibility study occurred and none are expected in the main study given the short duration of the study; however a 5% dropout is assumed and a sample size of 30 per group will be recruited.

### Measurement frequency

Clinical and implementation evaluations will be performed by the independent and trained research therapist at baseline, 3 weeks, 6 weeks, 9 weeks, and end of study (12 weeks) + 4 weeks FU for participants in both groups. Measurement instruments will be calibrated every month before the evaluation sessions and will be administered in a randomized sequence. Independent evaluation sheets will be used for each patient at each assessment session in order to minimize recording bias. All measurements will be performed through the use of electronic self-reported questionnaires on a laptop using the survey website. The evaluations will take approximately 60 min to complete and will be performed in a private assessment room located at University of Ottawa to optimize blinding of the evaluator.

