### Study design

The study is a single blind, two-arm RCT with a parallel group design to compare two study groups: 1) a knitting intervention (Group 1) and 2) a waiting list control group (Group 2). The intervention period will be 12 weeks plus a follow-up at 4 weeks post-intervention to measure the retention effect. Since this RCT involves a physical intervention (i.e. knitting program), the therapist, participants, and research coordinator administering the program will not be blinded. A blinded independent assessor will be trained to assess the participants though performance evaluation and self-reported questionnaires given at baseline, 3,6,9,12-week as well as at 4-week follow-up to reduce detection bias. With training and standard operating procedures, it is anticipated that any performance bias due to unblinding will be minimized. The study design flow chart is presented in Fig. 1. The study protocol is approved by the University of Ottawa Research Ethics Board (#H02–16-12).

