**Hand activity**
***level***, using an adapted 7-Day Physical Activity Readiness (PAR) [65–67] was used. The 7-day PAR is a validated instrument in a calendar format in which a participant can indicate the PA duration (minutes per day) and PA frequency (days per week). An adapted version of the 7-day PAR will be included in the logbooks where physical activity is split into distinct Knitting and other hand activities categories. The logbooks will also include a daily visual analogue scale for morning stiffness and pain intensity before and after knitting, information about hand physical activity level and knitting technique as well as a weekly questionnaire on actual changes in PA, medication intake (not encouraged), habits and adverse events. A similar logbook was created for PA activity other than knitting recording for the participants in the control group 2. ***Patient global assessment*** will be evaluated by asking patients if their condition after knitting program “fully improved”, “partially improved”, “did not improve” or “was worse compared to the beginning of the study” [31]. ***Health-related QoL*** will be assessed using the EuroQoL Index (EQ-5D-5 L) [68] including mobility, self-care, usual activities, pain/discomfort and anxiety/depression subscales.

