### Implementation outcomes

The following implementation outcomes are not represented in the OMERACT framework (fig. 2). ***Self-efficacy*** will be assessed using The Stanford Arthritis Self-Efficacy Scale (ASES) [33], a ten-point scale ranging from one (very uncertain) to 10 (very certain). Level of ***knitting enjoyment*** will be measured using Physical Activity Enjoyment Scale (PACES) for participant in group 1 only [70]. ***Adherence to PA/knitting program*** will be estimated as the number of knitting sessions attended at the Club and performed at home divided by the number of knitting sessions prescribed (84 sessions), as recorded in the participants’ logbooks, using the 7-Day PAR calendar [65] as well as attendance at the senior’s club. The number of wool squares that were knitted will be also reported in the participants’ logbooks. However, knitting technique will be recorded how the participants hold the stabilizing and mobile needle and which hand is used by the trained OT. Adverse events observed will be also compiled. All these clinical and implementation outcomes measures were pilot tested [43].

Please insert Table 1 Assessment schedule for primary, and secondary outcome measures.

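### The blinded assessor's sessions include an enjoyment scale given to Group 1 only, so from week 3 their content may reveal the arm when grip, pinch and physical function are tested

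*Protocol article*

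**What the plan says.** Under Study design, the therapist delivering the program, the participants and the research coordinator are all unblinded. Masking rests on one role: "A blinded independent assessor will be trained to assess the participants though performance evaluation and self-reported questionnaires". The stated purpose is to reduce detection bias.

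Measurement frequency gives this person's remit at all six visits: "Clinical and implementation evaluations will be performed by the independent and trained research therapist at baseline", then weeks 3, 6, 9 and 12 and the 4-week follow-up. That this is the blinded role follows from the same section, which says the evaluations "will be performed in a private assessment room located at University of Ottawa to optimize blinding of the evaluator".

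Implementation outcomes lists self-efficacy, knitting enjoyment and adherence. Enjoyment "will be measured using Physical Activity Enjoyment Scale (PACES) for participant in group 1 only". Table 1 repeats the Group 1 restriction and marks the scale in the columns for weeks 3/6/9, week 12 and follow-up, but not at baseline. Grip and pinch strength and FIHOA are marked in those same columns as well as at baseline.

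Measurement frequency also says that questionnaires are self-completed electronically on a laptop through a survey website, and that separate sheets are used for each participant and session.

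**The concern.** The plan promises a blinded evaluator and, as written, gives that evaluator a task that exists in one arm only. Someone who runs the session and can see whether PACES is among the forms knows the arm: its presence marks Group 1 and its absence marks Group 2.

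This matters most where the assessor can influence the result. Grip and pinch readings depend on effort, and encouragement can vary with what the tester expects. Under Strengths and limitations, the article offers performance-based measures, naming FIHOA, as a counterweight to imprecise self-report. That counterweight works only if the person administering them does not know the arm. Statistical analysis compares hand and finger strength and physical function between arms as secondary outcomes, so a tester's expectation would enter those comparisons as an apparent treatment effect.

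**Working it through.** The article gives no figure to reproduce. The check sets its sections side by side and counts visits.

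1. **Who is blinded.** Study design: only the independent assessor.
2. **What that person does.** Study design gives performance tests and questionnaires. Measurement frequency gives clinical and implementation evaluations. The two sections agree and describe the same role.
3. **What differs by arm.** Implementation outcomes and Table 1: PACES is for Group 1 only. It is the only row of Table 1 with a group restriction.
4. **When it differs.** The visits are baseline, weeks 3, 6, 9 and 12, and follow-up, which makes 6. PACES is marked at weeks 3, 6, 9 and 12 and at follow-up, which makes 5. So 5/6 = 83% of visits have different content by arm, starting at week 3. Baseline is unaffected.
5. **How many sessions that is.** With 30 recruited per group (Sample size calculation), the planned sessions number 60 × 6 = 360 before dropout. Of these, 60 × 5 = 300 fall at visits where the form set differs: 30 × 5 = 150 with PACES and 150 without. This counts opportunities for unblinding. It does not estimate how often unblinding would occur.
6. **What is measured at those visits.** Table 1 marks grip and pinch strength and FIHOA at all 5. Performance-based clinical outcomes treats FIHOA as a performance measure. The same section gives disease activity to a therapist from the Arthritis Society, who may be a different person, so the point is weaker for that outcome.
7. **What safeguards are stated.** Laptop self-completion might hide the form, but nothing says the evaluator is kept from seeing which forms are given. Strength cannot be self-reported, so the evaluator is in contact with the participant at the same visit. The private room shields the session from outsiders and does not hide a form from the person running it. Separate sheets address recording bias. No section gives PACES to an unblinded person or another session, or places it after the physical tests.

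**The case against.** The strongest counter-argument is that the questionnaires are a web survey completed by the participant, so the assessor may never see which forms appear. Study design also mentions training and standard operating procedures, and a condensed article may leave form handling to those. This stands in part: it makes unblinding likely rather than certain. It does not remove the point, because the article expressly gives the implementation evaluations to the blinded role.

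A reader might infer more than the text supports in five ways:

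- **That allocation is certainly disclosed from week 3.** The article does not say who opens or sees the forms.
- **That collecting adherence also unblinds the assessor.** Table 1 marks adherence at the visits, but Implementation outcomes takes it from logbooks and club attendance, and under Intervention the knitting instructor checks that logbooks are properly filled in. Nothing says the assessor reviews them.
- **That the patient global item gives the arm away.** It "will be evaluated by asking patients if their condition after knitting program" has changed, which is awkward for controls. Table 1 has no group restriction on this item, so being given it does not identify an arm.
- **That random ordering puts PACES ahead of strength testing.** Instruments "will be administered in a randomized sequence", but the subject of that sentence is instruments calibrated monthly, which may mean physical devices only. The order of questionnaires relative to strength tests is simply not fixed.
- **That the primary result is compromised.** Daily stiffness is scored by participants who already know their arm, so assessor unblinding does not directly touch it. AUSCAN, EQ-5D and self-efficacy are likewise self-reported.

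It is also fair to say that participants may disclose their arm in conversation. That is no reason to build a further cue into the schedule.

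**Conclusion.** The concern holds as a risk to assessor blinding. The plan gives its only blinded role an evaluation set that differs by arm at 5 of 6 visits, without a stated safeguard sufficient to conceal the difference. The detection-bias risk is confined to assessor-measured secondary outcomes, chiefly grip and pinch strength and FIHOA.

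This rests on two assumptions: that the research therapist under Measurement frequency is the blinded assessor under Study design, which the wording of both supports, and that the therapist can tell which questionnaires a participant receives, which is plausible but not stated. If an operating procedure already hides the forms, the point reduces to saying so. The documents give no basis for estimating the size of any bias. The change is worth making because it is cheap and protects the only masking this design allows.

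**What to change.** 1. Take PACES out of the assessor's session. Have Group 1 complete it remotely on the survey website already in use, around weeks 3, 6, 9 and 12 and follow-up. Do not route it through the research coordinator, whom Group assignment describes as not involved in data collection. Collection at the club is also unreliable at follow-up, because after week 12 only those who improved are encouraged to continue.
2. State that the blinded assessor does not handle adherence, club attendance or logbook data.
3. Fix the order within each visit: dynamometry and physical function tests first, then questionnaires. Any randomized sequence can be kept within each block.

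This needs no extra staff or visits. Remote completion may leave slightly more missing PACES data. That is a small price, since the scale is collected in one arm only and so supports no between-group comparison.

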### Statistical analysis

Descriptive statistics will be used to summarize the study variables and to assess the distributional assumptions of the statistical techniques used. An intention to treat analysis will be conducted for all the data analyses.

A per protocol analysis will be considered as part of the sensitivity analyses. The primary outcome is the area under the curve (AUC) at 2 h for stiffness. That is, stiffness at 2 h post-awakening from sleep will be assessed each day for 12 weeks, and the AUC over this 12 week period will then be calculated. Similar AUCs will be calculated for stiffness at 0 h (at awakening), 4 h (post-awakening) and evening. Also, similar AUCs for the secondary outcomes pain and function will be calculated.

For the primary outcome (AUC at 2 h for stiffness) participants in the knitting group will be compared to participants in the control group using independent Student’s t-test with the pooled or separate variance estimate as appropriate. For the primary and secondary outcomes, the area under the curve (AUC) for stiffness, pain and function will be compared using a 2-way analysis of variance (ANOVA) with the between factor group (knitting vs control) and within factor time (0 h, 2 h, 4 h, evening). Tukey’s [71] honest significance difference (HSD) will be used to make specific pairwise comparisons. The secondary outcomes, AUSCAN overall, AUSCAN pain, AUSCAN stiffness, AUSCAN function, hand and fingers strength and physical function, self-efficacy, hand physical activity level and adherence, global patient improvement as well as QoL will be compared using a 2-way analysis of variance (ANOVA) with the between factor group (knitting vs control) and within factor time (baseline, 3 wk., 6 wk., 9 wk., 12 wk. and 4-wk Follow-Up). Again, Tukey’s HSD [71] will be used to make specific pairwise comparisons. As a secondary analysis, additional time assessments to 16 weeks will be included in the above analyses to assess follow-up. An alpha significance of 0.05 was chosen for all analyses. Mixed models repeated measured will be used to accommodate missing data. No interim efficacy or subgroup analyses are planned.

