### Inclusion/exclusion criteria

To be eligible for this RCT, participants will be required to: 1) meet the ACR clinical and radiographic criteria of definite HOA and of mild to moderate severity status [50] and have experienced pain symptoms for at least 3 months, 2) be between 50 and 85 years of age, 3) have a level of morning stiffness of at least 4/10 on a visual analogue scale (VAS) [53] at the time of study entry, 4) display X-ray evidence of joint space narrowing of the hands [51], 5) have no knowledge of knitting (do not know how to knit) or have not knitted in the last 2 months; 6) be available for sessions at the senior’s club twice a week, 7) be able to understand written and verbal English instructions. Participants will be excluded if they: 1) are current active knitters; 2) are unwilling or unable to adhere to the knitting program for 12 consecutive weeks, 3) have other orthopedic, rheumatologic diseases (i.e. inflammatory arthritis, psoriasis arthritis, gout…), or evidence of chondrocalcinosis, 4) had any prior surgery for the finger joints, 5) have any acute disease, such as uncontrolled diabetes mellitus, untreated hypertension, neurological deficits (motor or sensory) or cognitive deficit and mental health conditions, 6) are taking OA medication that is expected to change during the study period, 7) receiving current rehabilitation treatment or any other pain-related treatment besides medication for OA, 8) have received corticosteroid injection of finger joints within the last 6 months, 9) plan to move or relocate within 6 months.

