### Self-reported and performance-based clinical outcomes outcome measures (Table 1)

The clinical outcomes were selected according to the OMERACT framework illustrated in Fig. 2 and include the followings:

**Table 1 Tab1:** Assessment schedule for primary, and secondary outcome measures

Assessment	Admission	Daily	Baseline	3/6/9 weeks mid intervention	12 weeks end of intervention	4 weeks follow-up
Informed consent (pre-admission)	X					
Diagnosis of HOA based on ACR criteria	X					
Socio-demographics	X					
Edinburgh Handedness Inventory	X					
Self-reported daily morning stiffness intensity (Visual analogue scale: VAS) (primary daily outcome)	X	X	X	X	X	X
Self-reported daily pain intensity (VAS) (intermediate daily outcome)	X	X	X	X	X	X
Pain intensity (Auscan) (periodic secondary measurement)			X	X	X	X
Morning stiffness severity (Auscan) (periodic secondary outcome)			X	X	X	X
Hand functional status/difficulty in activities of daily living (Auscan) (periodic secondary outcome)			X	X	X	X
Disease activity status (periodic secondary outcome)			X	X	X	X
Dynamometric strength measurements (Grip and pinch measurements) (periodic secondary outcome)			X	X	X	X
The Functional Index for Hand Osteoarthritis (FIHOA) (periodic secondary outcome)			X	X	X	X
Hand physical activity level (periodic secondary outcome)		X	X	X	X	X
Patient global assessment (periodic secondary outcome)			X	X	X	X
Quality of life (EQ-5D) (periodic secondary outcome)			X	X	X	X
Self-efficacy (periodic secondary outcome)			X	X	X	X
Physical Activity Enjoyment Scale (PACES) (Group 1 only)				X	X	X
Adherence to knitting program (Daily secondary outcome)			X	X	X	X
7-day Physical Activity Recall (PAR) (Daily secondary outcome)			X	X	X	X

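### The primary t-test on 12-week stiffness AUC leaves out a stiffness VAS collected before randomisation; it is valid and adequately powered, but gives up precision and leaves chance baseline imbalance uncorrected

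*Protocol article*

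**What the plan says.** The Statistical analysis section defines the endpoint: "The primary outcome is the area under the curve (AUC) at 2 h for stiffness". It is built from readings taken 2 h after waking on every day of the programme. No subtraction of a baseline value is described. For this endpoint, "participants in the knitting group will be compared to participants in the control group using independent" samples methods. The test is named in full as an "independent Student’s t-test with the pooled or separate variance estimate as appropriate", and no covariate is mentioned.

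Nothing else in that section brings in baseline stiffness:

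- The two-way ANOVA of the AUCs has group and a "within factor time (0 h, 2 h, 4 h, evening") as its factors.
- Baseline appears only as one of the time levels for the periodic secondary outcomes, such as AUSCAN.
- The mixed model is mentioned for one purpose: "Mixed models repeated measured will be used to accommodate missing data".

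A starting value is nevertheless available. The Inclusion/exclusion criteria require participants to "have a level of morning stiffness of at least 4/10 on a visual analogue scale (VAS") at entry. The Recruitment section collects stiffness intensity in the eligibility questionnaire, before randomisation. Table 1 marks the row "Self-reported daily morning stiffness intensity (Visual analogue scale: VAS) (primary daily outcome") at both admission and baseline. Under Group assignment, randomisation is 1:1 in blocks varying between 4 and 6, and no stratification by stiffness is stated.

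**The concern.** An AUC of raw daily scores reflects where each woman started as well as what the programme did. So far as starting stiffness predicts the later AUC, an unadjusted comparison leaves that predictable variation in the error term. A chance difference between arms at entry also carries over, in part, into the estimated effect. Neither the randomisation nor the stated primary analysis controls for it.

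In a trial of 60 people with a single primary comparison, moderate imbalance is common. A reader who sees it in the baseline table will ask whether it explains the result. Adjustment chosen only after the data have been seen is a much weaker answer than adjustment fixed in advance.

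**Working it through.** **Inputs.** From Sample size calculation: effect 0.8 SD, power 80%, significance level 0.05 (sidedness not stated; two-sided assumed), 28 per group, 5% dropout, 30 per group recruited. The documents give no correlation ρ between pre-randomisation VAS and 12-week AUC, so ρ is an assumption, shown over a range.

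**The plan's own figure.** A two-sided two-sample t-test (noncentral t) with d = 0.8 and 80% power needs n = 25.5, so 26 per group. The stated 28 is within two of this and on the safe side. Allowing for dropout, 28 / 0.95 = 29.5, so 30 per group, as stated.

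**Power of the planned t-test at 28 per group.** Noncentrality = 0.8 × √(28/2) = 2.99 on 54 degrees of freedom, which gives 83.6%. The difference detectable with 80% power is 0.76 SD.

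**ANCOVA with one baseline covariate.** The residual variance is multiplied by (1 − ρ²). The variance of the group contrast is also multiplied by 1 + 1/(2n − 4), which allows for chance covariate imbalance, and the degrees of freedom are 2n − 3 = 53. The noncentrality is

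d / √[(1 − ρ²) × (2/n) × (1 + 1/(2n − 4))].

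At n = 28 and ρ = 0.5 this is 0.8 / √(0.75 × 0.0714 × 1.0192) = 3.42, which gives 91.9%. Over the range:

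| Analysis | Power at d = 0.8, 28 per group | Detectable difference at 80% power | n per group for 80% power |
|---|---|---|---|
| t-test | 83.6% | 0.76 SD | 26 |
| ANCOVA, ρ = 0 | 82.9% | 0.77 SD | 27 |
| ANCOVA, ρ = 0.3 | 86.2% | 0.74 SD | 24 |
| ANCOVA, ρ = 0.5 | 91.9% | 0.67 SD | 20 |
| ANCOVA, ρ = 0.7 | 98.3% | 0.55 SD | 15 |

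**Chance imbalance with 30 per arm.** The standard error of the baseline difference is √(2/30) = 0.258 SD. The probability of an absolute difference above 0.25 SD is 2 × [1 − Φ(0.25/0.258)] = 33%. Above 0.5 SD it is 2 × [1 − Φ(0.5/0.258)] = 5%. Given a baseline difference of 0.25 SD, the unadjusted contrast shifts by ρ × 0.25: 0.075, 0.125 or 0.175 SD for ρ = 0.3, 0.5 or 0.7. Against the planned effect of 0.8 SD, that is roughly 9% to 22%.

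**The case against.** The strongest reply is that nothing here is wrong. Under 1:1 randomisation the t-test is unbiased over repeated randomisations and holds its type I error, and its standard error already allows for chance imbalance. It matches the sample size calculation and exceeds the 80% target. All of that stands. A reader might infer that the primary analysis is invalid or the trial underpowered because baseline is left out; the protocol's own figures do not support this.

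A reader might also suppose that a baseline difference passes in full into the estimate. Only the fraction ρ does, and only the fraction ρ² of the variance can be removed.

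The gain may be small. The entry floor of 4/10 and the restriction to mild to moderate disease narrow the baseline range. The protocol does not say that the admission or baseline VAS is taken at 2 h after waking, as the endpoint is. The pilot 2 h AUC averaged 0.188 of its maximum, about 1.9 on the 10-point scale and well below the entry floor. Pilot entry criteria are not shown in the text at hand, so this is only suggestive, but it fits entry stiffness and 2 h stiffness being different quantities. Nothing supports ρ = 0.7 in particular, and the 98% should not be read as an expected result.

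Finally, this is a condensed article, and an unseen SAP may list covariates for the mixed models. It is therefore not shown that baseline is ignored everywhere. That does not alter the primary test, which the article names explicitly.

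**Conclusion.** The point holds as a matter of efficiency and robustness, not validity. The primary test is fixed as an unadjusted comparison although a pre-randomisation measure of the same symptom is available for every participant at no extra cost. The benefit depends on an unknown correlation: at 28 per arm and d = 0.8, about 3 percentage points of power at ρ = 0.3, 8 at ρ = 0.5 and 15 at ρ = 0.7, with the lower end perhaps more likely. The price if the covariate proves useless is 0.7 of a point. That asymmetry, and the one-in-three chance of an imbalance above 0.25 SD, justify the change.

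The open choice between pooled and separate variance is a minor matter. With equal arms the two t statistics coincide and only the degrees of freedom differ. It would be wrong to read that wording as a serious threat to the result, though one rule should still be stated.

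**What to change.** In Statistical analysis, replace the primary t-test with an ANCOVA of the 12-week 2 h stiffness AUC on group, with the pre-randomisation stiffness VAS as covariate. In addition:

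- State which reading is used, admission or baseline visit, confirm that it precedes randomisation, and record its time of day. Exclude the daily pre-knitting reading, which the section on self-reported clinical outcomes also labels baseline: it is taken after randomisation and could be affected by treatment.
- Prespecify one variance estimate valid under unequal variances, such as a small-sample robust standard error, in place of a choice between pooled and separate.
- Report the adjusted mean difference with its 95% confidence interval.
- Keep the unadjusted t-test as a sensitivity analysis.

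The sample size can stay as it is. The cost is a change of wording and a clear definition of the covariate, made before any outcome data are seen by arm. No extra visits, measurements or participants are needed.
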